### Specific objectives

To measure the decrease in volume of the affected limb treated with TAPA and the maintenance of the effect over time (1 month and 3 months).To evaluate its effect on the performance of activities of daily living (ADL).To evaluate its effect on health-related quality of life (HRQOL).To determine efficiency in terms of simplicity of handling and economy of the anti-edema bandage technique used in the TAPA group.

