### Sample size

It is agreed that a decrease in the volume of the clinically relevant lymphedema may be established at 150 ml. (minimal detectable value) [39], 20% with respect to the baseline. Based on data from the literature on means and standard deviations [25, 40], for an alpha error of 0.05 and a statistical power of 0.80, the necessary sample size would be 29 subjects per group (calculation performed with EPIDAT 4.2). It is assumed that the standard treatment effect in the control group will lead to a reduction in arm volume by an average of 5%, the treatment effect in the experimental group will cause an average reduction in arm volume of 20%, and the standard deviation will be similar in both groups, approaching 20% [41]. Taking into account the dropout rate of 10% in each group, the corrected sample size is 64 patients, randomly assigned to two groups with 32 patients each.

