### Statistical analysis

Analysis is performed for intent to treat. Data lacking after the basal measurements are replaced using the last available observation. Quantitative and qualitative variables will be described as usual (mean, standard deviation; proportions). An analysis of basal comparability of the sociodemographic and clinical variables **(**Table 1**)** will be carried out between both treatment groups. Then, a bivariate analysis will be conducted, previously verifying that the quantitative variables follow a normal distribution, using the Kolmogorov-Smirnov or Shapiro-Wilk tests, in which case, a repeated measures ANOVA is carried out (Mixed Models), to analyze the profile of patients from the basal measurement (24–72 h before treatment onset), after completing 10 sessions and one and 3 months later. If the variables do not follow a normal distribution, non-parametric tests will be used (Friedman’s test). In addition, a multivariate analysis will be performed, as well as a survival analysis, Cox regression or multiple linear regression, taking into account the examined sociodemographic and clinical covariables resulting statistically significant following the bivariate analysis, for their inclusion in the model or to be controlled for, given their potential confounding effect. The main dependent variable will be the reduction of volume of the affected extremity. Statistical analysis will be performed using the Statistical Package for the Social Sciences (SPSS v.17). Statistical significance values will be those normally used (*p* < 0.05) and bilateral contrasts will be carried out. To evaluate effectiveness, a comparative analysis of economic costs of both treatments will be performed.

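### The volume analysis makes baseline one of four response visits and does not say which model term or visit tests TAPA against control; a single baseline-adjusted difference would match the sample size and gain power

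*Protocol article*

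**What the plan says.** The Statistical analysis section states that "a repeated measures ANOVA is carried out (Mixed Models), to analyze the profile of patients from the basal measurement", then after the 10 sessions and at 1 and 3 months. The end of the Interventions section repeats this four-point profile. The response is identified as follows: "The main dependent variable will be the reduction of volume of the affected extremity". Tests are two-sided at the 5% level. Later multivariable models take sociodemographic and clinical covariates that prove significant in the bivariate analysis. Table 1, which lists those variables, contains stage but not baseline limb volume.

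The Sample size section says that "for an alpha error of 0.05 and a statistical power of 0.80, the necessary sample size would be 29 subjects per group". It assumes that "the standard treatment effect in the control group will lead to a reduction in arm volume by an average of 5" per cent, that "the treatment effect in the experimental group will cause an average reduction in arm volume of 20" per cent, and that "the standard deviation will be similar in both groups, approaching 20" per cent. The Expected results section also frames the aim between arms: a reduction at least 150 ml larger than in the control group. The first specific objective covers the decrease in volume and "the maintenance of the effect over time (1 month and 3 months" after treatment.

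**The concern.** A repeated measures ANOVA with two arms and four visits produces several tests, and they answer different questions.

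- The time effect does not compare the arms.
- The group main effect compares the arms, but averages in the baseline visit, where randomised arms have no expected difference, and is tested against the full between-patient variation.
- The group-by-time interaction, on 3 df, shows that the profiles differ somewhere, but not at which visit or in whose favour.

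The section does not say which of these decides whether TAPA reduces volume more than control, nor at which visit. The choice could be made after the data are seen, and the stated 80% power is not tied to any of them. In addition, baseline volume, which is measured in every woman, is not used as a covariate.

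**Working it through.** **Inputs from the Sample size and Statistical analysis sections.** Difference 20 − 5 = 15 points; SD 20; two-sided alpha 0.05; 29 per group; four visits including baseline.

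**Assumptions not in the article.** The SD of 20 is the SD of change from baseline, and volume is scaled in the same percentage points. The four visits have equal variance σ² and common correlation ρ (compound symmetry). The SD of change then fixes σ²: 2σ²(1 − ρ) = 400, so σ²(1 − ρ) = 200.

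**1. The plan's own figure.** Two-sample t-test of reduction: noncentrality 15 / (20·√(2/29)) = 2.856, 56 df, critical value 2.003, power 80.1%. With 28 per group, power is 78.7%. So 29 per group is reproduced, for a comparison of change at one visit.

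**2. Group-by-time interaction, 3 and 168 df.** Noncentrality = (29/2)·Σ(d − d̄)² / 200, where d is the between-arm difference at the four visits. Given the SD of change, ρ cancels.

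| Differences at baseline, end, 1 month, 3 months | Σ(d − d̄)² | Noncentrality | Power |
|---|---|---|---|
| 0, 15, 15, 15 | 168.75 | 12.23 | 84% |
| 0, 15, 7.5, 0 | 154.69 | 11.21 | 80% |
| 0, 15, 10, 5 | 125.00 | 9.06 | 70% |

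**3. Group main effect over four visits.** For a sustained effect, the averaged difference is (0 + 15 + 15 + 15)/4 = 11.25. The SD of a patient's four-visit mean is σ·√((1 + 3ρ)/4).

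| ρ | SD of mean | Power, sustained effect |
|---|---|---|
| 0.3 | 11.6 | 95% |
| 0.5 | 15.8 | 76% |
| 0.7 | 22.7 | 46% |
| 0.8 | 29.2 | 30% |
| 0.9 | 43.0 | 17% |

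**4. Baseline-adjusted difference at one visit.** Residual variance is σ²(1 − ρ²) = 200(1 + ρ), against 400 for the change score. Power is by noncentral t with 55 df, 29 per group; any further gain from stage is not counted.

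| ρ | Residual variance | Residual SD | Power | Per group for 80% |
|---|---|---|---|---|
| 0.5 | 300 | 17.3 | 90% | 22 |
| 0.7 | 340 | 18.4 | 86% | 25 |
| 0.8 | 360 | 19.0 | 84% | 27 |
| 0.9 | 380 | 19.5 | 82% | 28 |

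At every ρ shown, the adjusted comparison exceeds the 80.1% of the unadjusted change score. The margin falls from about 10 points of power at 0.5 to about 2 at 0.9.

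**The case against.** Four points can be made for the plan, and most of them limit the concern.

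- **The between-arm aim is stated.** Sample size and Expected results both define a difference between the arms. A reader might infer that the protocol has no treatment comparison at all; that is not so. What is missing is the link from that aim to a model term and a visit. An analysis plan could supply the link, but the article already commits to a model, a baseline response visit and a covariate rule, and a plan that followed it would inherit them.
- **The severe power loss is not what the protocol prescribes.** A reader might infer that the trial is badly underpowered. The low figures apply only if the group main effect is read, and nothing in the article says it will be. Analysing a profile points more naturally to group-by-time, where power is 84%, 80% or 70%.
- **Baseline as a response is accepted practice in mixed models.** The treatment contrast in change from baseline to one visit is the comparison the trial was sized for. If the arm means are constrained equal at baseline, such a model also keeps the precision of covariate adjustment. This stands, but the article states neither the contrast nor the constraint.
- **Severity at baseline is partly covered.** Stage is defined by volume difference, is the randomisation stratum and appears in Table 1. It is, however, a coarse two-level proxy, and it enters only if significant.

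A reader might also infer that the ANOVA fails outright, because a reduction is zero for every woman at baseline. That takes the named main variable as the modelled response. Table 2 records volume in ml and per cent, so measured volume profiled over visits is the more natural reading. The wording is loose, but no breakdown of the model is shown.

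**Conclusion.** The concern holds as a specification gap with a cheap and better alternative. The sample size arithmetic is sound, but its 80% belongs to a two-sample comparison of change at one visit, and the analysis section names neither that test nor any other as decisive. The planned model does not necessarily have less power: group-by-time is at or above 80% for two of the three effect patterns examined and 70% for the third. Its weakness is that a significant result would not by itself show that TAPA did better, or when.

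Adjusting for baseline volume raises power at 29 per group to about 90% at ρ = 0.5 and 82% at ρ = 0.9. These figures rest on an assumed correlation, compound symmetry, and reading the SD of 20 as that of change. The gain should not be presented as large whatever the correlation: at 0.9 it is 5% of the variance (380 against 400).

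**What to change.** In the Statistical analysis section, model the three post-baseline volumes with treatment, visit and treatment-by-visit, and with baseline volume (in the same metric) and stage as covariates fixed in advance. An equivalent mixed model with baseline as a response and the arm means constrained equal at baseline would serve as well. Name as the main test the 1-df baseline-adjusted TAPA-minus-control difference at one prespecified visit, and tie the sample size statement to it. End of treatment is a natural choice, but the choice is the sponsor's. Report the adjusted differences at the other visits with 95% confidence intervals to answer the maintenance objective.

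This takes one or two sentences and needs no new data, visits or patients. The price is that the visits not chosen become secondary.

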### Objectives

This study aims to verify both the efficacy of the new therapy (TAPA) versus conventional treatment, as well as its efficiency in terms of cost-effectiveness, in patients suffering from Breast Cancer-Related Arm Lymphedema (BCRAL).

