## Methods

### Design

Controlled clinical trial, randomized by stratification in two gradients, with two parallel arms, longitudinal and single blind. To measure the efficiency of the new treatment, a cost-effectiveness study will be performed [34–36] .

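### The only test named for non-normal data, Friedman's test, has no treatment term, so the stated fallback does not compare TAPA with control

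*Protocol article*

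**What the plan says.** The Design section describes a "Controlled clinical trial, randomized by stratification in two gradients, with two parallel arms, longitudinal and single blind", and the Objectives section states that "This study aims to verify both the efficacy of the new therapy (TAPA) versus conventional treatment". The Sample size section powers the trial on a difference between the arms in mean volume reduction.

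The Statistical analysis section states that "The main dependent variable will be the reduction of volume of the affected extremity". It sets a two-way rule for quantitative variables. Normality is checked "using the Kolmogorov-Smirnov or Shapiro-Wilk tests, in which case, a repeated measures ANOVA is carried out (Mixed Models"), applied to four visits: baseline, after the 10 sessions, and one and three months later. Otherwise, "If the variables do not follow a normal distribution, non-parametric tests will be used (Friedman’s test"). No other non-parametric test is named anywhere in the article.

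The section then adds: "In addition, a multivariate analysis will be performed, as well as a survival analysis, Cox regression or multiple linear regression", adjusted for covariates that were significant in the bivariate step. The comparisons it explicitly places between the two treatments are baseline comparability, which "will be carried out between both treatment groups", and costs.

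**The concern.** The two branches are not equivalent. A repeated-measures ANOVA or mixed model can carry group and group-by-time terms, and so can answer the trial's question. Friedman's test is a one-sample test across visits. Run in each arm, it shows whether that arm changed over time. Run on both arms together, it ignores treatment altogether. A failed normality test would therefore change the question as well as the method.

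The gate is also set on the variables themselves. What a mixed model needs is roughly normal residuals. A variable can fail a normality test, for instance because two severity stages are pooled, while a model that includes stage fits acceptably.

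At stake is the main efficacy comparison. If only within-arm results were available on that branch, the natural temptation would be to contrast a significant arm with a non-significant one. That does not compare the randomised groups and does not hold the 5% level.

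**Working it through.** **1. The planned question is between arms.** Inputs from the Sample size section: reductions of 20% and 5% (difference 15), SD 20, two-sided alpha 0.05, power 0.80.

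- Normal approximation: n = 2(1.960 + 0.842)² × 20² / 15² = 2 × 7.85 × 1.778 = 27.9, so 28 per group.
- Two-sample t-test: n = 28.9, so 29 per group, with power 0.801 at 29.

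This reproduces the stated 29. The stated 32 per group follows as 29 × 1.10 = 31.9. The trial is thus sized for a two-sample comparison.

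**2. What Friedman's test uses.** With n patients, k = 4 visits and R_j the sum over patients of the within-patient ranks at visit j:

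Q = 12 / [n k (k + 1)] × Σ R_j² − 3 n (k + 1)

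No term refers to treatment. As a check on simulated data for 58 patients, Q was 1.6966 before and after patients were shuffled across arms.

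**3. What it does when the arms are equal.** Simulation with 29 per arm, four visits, SD of change 20, the same mean reduction at all three follow-up visits, and normal data. The correlation among the three follow-up changes was varied from 0.4 to 0.8. The documents give neither this correlation nor the course over time, so both are assumptions. TAPA only means Friedman significant in the TAPA arm and not in the control arm.

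| True reduction in both arms | Friedman significant, each arm | Friedman significant, arms pooled | TAPA only |
|---|---|---|---|
| 5% | about 19% | about 36% | about 15% |
| 10% | about 61–66% | about 90–95% | about 23% |
| 15% | about 93–96% | over 99% | about 4–7% |
| 20% | over 99% | 100% | under 0.5% |

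The last column has a simple form. For two independent arms with the same rejection probability p, P(TAPA only) = p(1 − p). With p = 0.64 this is 0.64 × 0.36 = 0.23; with p = 0.19 it is 0.19 × 0.81 = 0.15. It cannot exceed 0.25, reached at p = 0.5. The comparator is 2.5%, the share of a two-sided 5% test that favours TAPA.

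**4. A between-arm rank test at the same size.** A Mann-Whitney test on change from baseline at one visit rejected in about 4.4–5.4% of runs when the arms were equal. At 20% against 5% its power was about 0.77–0.78.

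**The case against.** Four points can be made for the plan.

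- **The additional regression.** It does not depend on the normality result. Table 1 lists treatment group among the independent variables, and adjusting for confounding most naturally refers to the treatment effect. A reader might infer from the Friedman rule that efficacy goes untested on that branch. The document does not support that, because a regression with group may be intended. But no treatment term, outcome visit or model is written for it, and several alternatives are listed side by side. It does not clearly supply the comparison.
- **The wording is plural.** The parenthesis may give only the rank counterpart of the time-profile analysis. That softens the point. Still, the one test named is not a between-arm test, so this is more than detail left to an analysis plan.
- **The error rates rest on a rule the protocol does not contain.** This stands. Nowhere does it say that efficacy will be claimed when one arm is significant and the other is not. A reader might take 23% or 25% as the trial's false-positive rate. It is not: it is conditional on that inferred rule, lies close to the 25% ceiling, and falls below 0.5% when both arms improve by 20%.
- **The branch may not be reached.** This also stands. The documents do not say how the outcome is distributed, and the simulated data were normal, so the figures describe what follows if the branch is used, not how often it is used.

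**Conclusion.** The point holds in this form: the named non-parametric fallback does not test TAPA against control, although that is what the trial is designed and sized to test. This follows from the structure of Friedman's test and needs no assumption.

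The size of the consequence does need assumptions. If efficacy were read from within-arm results, the chance of a spurious finding for TAPA would range from under 0.5% to about 23% over the equal reductions of 5% to 20% examined, against a nominal 2.5%. That range rests on 29 per arm, SD 20%, a constant effect over follow-up and correlations of 0.4–0.8. The defect is limited to the non-normal branch, and the planned regression may partly cover it if it includes group.

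**What to change.** In the Statistical analysis section:

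1. Keep the mixed model as the main analysis and judge it on its residuals. Drop the normality test of the variables as the switch between methods.
2. State its terms: group, time, group-by-time and stage. Enter baseline either as a covariate, with only the follow-up visits as response, or as one of the response visits, but not both. The present text treats baseline as a visit in the profile.
3. For clearly non-normal residuals, replace Friedman's test with a between-arm method. One option is a stage-stratified Wilcoxon (van Elteren) test on change from baseline at one pre-specified visit, for example after the 10 sessions. Another is a permutation or bootstrap interval for the difference between arms.
4. Retain Friedman's test, if wanted, only as a within-arm description.

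The cost is a few sentences and no new data. If the rank test is used, power falls slightly, to about 0.77–0.78 against the planned 0.80. That figure comes from the unstratified rank test on normal data; the stratified version was not simulated.

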## Background

Breast cancer (BC) is a major public health issue, being the most common global cause of cancer-related deaths in females and the second most common form of cancer, with over 2 million new cases occurring in 2018 [1]. BC survival rates have improved notably over the past 20 years (survival from this type of tumor increases by 1.4% annually) [2]. BC survivors face challenges in their activities of daily living (ADL), as a result of both the illness and the subsequent treatments undertaken. These challenges include altered sensory and pain functions and neuromusculoskeletal and movement-related alterations, as well as alterations of the skin and related structures. These symptoms tend to continue for extended periods of time and therefore, BC survival has been categorized as a chronic illness with new challenges arising for rehabilitation services [3, 4].

It is estimated that more than one out of every five women treated for BC will develop lymphedema in an upper extremity (20% in 6 months, 36% in 1 year and 54% within 36 months). The most relevant risk factors are the number of lymph nodes excised in surgery, radiation therapy and obesity. This is a chronic and progressive disorder that causes edema, skin changes (which may cause fibrosis and deformity), pain, sensitivity alterations, fatigue, limitations in joint rotation, recurrent infections, an inability to independently carry out ADL, low self-esteem, etc. Although it has been recognized for years now, consensual treatment dose programs have yet to be established [5].

Tertiary prevention in BC attempts to combat the consequences of this illness. It includes aspects such as rehabilitation, relapse prevention, early diagnosis of second malignancies, management of late complications through treatments and emotional support. This type of assistance has been traditionally presented for some time now in specialized health care, but it is currently becoming an increasing primary care responsibility [6, 7].

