### Study variables and measurement instruments

The study variables are shown in Tables 1, 2, 3.

**Table 1 Tab1:** Independent study variables and their measurement instruments

INDEPENDENT VARIABLES (Sociodemographic and clinical variables)	MEASUREMENT INSTRUMENTS (to be filled in with information from interviews and clinical records)
- ID: Identification number for the study (1, 2, 3...)	ID:
- Age.	Date of bird _/_/_ _ years old
- Group (Treatment carried out):	TAPA / standard.
- Work activity:	Working (Which?) /Retired/Unemployed/Others (Which?)
- Menstrual situation:	Pre-menopausal/Post-menopausal
- Laterality:	Right/ left/Both
- Body mass index (BMI): - Obesity:	BMI: height/weight^2^ yes (BMI > =30)/ no (BMI < 30)
- AHT (Arterial hypertension):	Yes (> = 120/80 mmHg/take medication) / no (< 120/80 mmHg)
- DLP (Dyslipidemia):	Yes (> = 200 mg dl/take medication) / no (< 200 mg/dl)
- DM (Diabetes):	Yes (> = 126 mg dl/take medication) / no (< 126 mg/dl)
- Heart disease:	Yes / no
- Kidney failure: Yes / no	Yes / no
- Vascular disease: Yes /no	Yes / no
- Thyroid disease: Yes / no	Yes / no
- Pacemaker: Yes / no	Yes / no
- Electro-stimulator: Yes /no	Yes / no
- Date of BC diagnosis	_/_/_
- Date of lymphedema diagnosis	_/_/_
- Stage:	I, II
- Edema location:	Hand(H)/Forearm (F)/Arm (A)/ Breast H + F/ H + F + A/ F + A/ Complete/ Others (this category should be thoroughly considered)
- Breast:	Right/ left
- Date of surgical intervention:	_/_/_
- Type of tumor: - Intervention type: Conservative/mastectomy	ductal infiltrating/in situ/ lobular/ inflammatory/tubular/other (which?): Conservative/mastectomy
- Axillary surgery:	sentinel ganglion biopsy (SGB)/ lymphadenectomy /Both/none
- No. of excised ganglia:	N°
- No. positive ganglia:	N°
- Complications:	Infection/ hematoma/ seroma/nerve lesion/Axillary web syndrome
- Chemotherapy:	Yes / no
- Radiotherapy:	Yes / no
- Hormone therapy:	Yes / no
- Immunotherapy:	Yes / no
- Breast reconstruction:	Yes / no Yes: - Type of reconstruction: Prosthesis/back/ abdomen - Reconstruction time: Immediate/ deferred
- Date of symptom onset:	_/_/_
- Lymphedema:	Right/ left

**Table 2 Tab2:** Primary dependent study variables and their measurement instruments

PRIMARY DEPENDENT VARIABLES	MEASUREMENT INSTRUMENTS/INTERPRETATION OF RESULTS

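### Covariates for the additional adjusted regression are chosen by significance in the same data from 34 candidates in 64 women, so the model is left to chance and neither stage nor baseline volume is secured

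*Protocol article*

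**What the plan says.** The Statistical analysis section of the protocol article sets out three steps. First comes "An analysis of basal comparability of the sociodemographic and clinical variables" of Table 1 between the arms. A bivariate analysis follows, with a repeated measures ANOVA or mixed model over four time points. The third step is a regression: "In addition, a multivariate analysis will be performed, as well as a survival analysis, Cox regression or multiple linear regression". The rule by which covariates come into it reads "taking into account the examined sociodemographic and clinical covariables resulting statistically significant following the bivariate analysis, for their inclusion in the model". The same sentence then gives its reason, that such variables are "or to be controlled for, given their potential confounding effect". Significance is two-sided p<0.05. On the outcome, "The main dependent variable will be the reduction of volume of the affected extremity".

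The candidates are the variables of Table 1, headed "INDEPENDENT VARIABLES (Sociodemographic and clinical variables". No covariate is named in advance. Stage is one of the Table 1 items and also the stratification factor (Random allocation and concealment of allocation). It decides which control treatment a woman receives (Interventions). Limb volume appears in Table 2 as a dependent variable and is not in Table 1.

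**The concern.** This is a rule that the article states, not a detail left to an analysis plan. It imports confounder selection from observational research into a randomised trial, where a baseline difference between arms is a matter of chance and a significant one does not show that the variable predicts volume.

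Three things are at stake. The adjusted model is known only after the data have been seen and would differ from sample to sample. Covariates that ought to be in the model can be left out: stage may miss p<0.05, and baseline volume is never offered. And covariates selected by chance can cost precision or, under some forms of screening, absorb part of the treatment effect.

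**Working it through.** **Inputs from the protocol.** Sample size section: mean reductions of 5% and 20%, SD about 20%, "for an alpha error of 0.05 and a statistical power of 0.80", 29 per group, 10% dropout, 64 in total. Table 1: 36 items, or 34 without the ID and the treatment group.

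**The plan's own figure.** Standardised difference = (20 − 5)/20 = 0.75. Normal approximation: n = 2(1.96 + 0.8416)²/0.75² = 27.9, so 28 per arm. With the exact noncentral t, power is 0.787 at 28 and 0.801 at 29, so 29 is reproduced. 29 × 1.10 = 31.9 gives 32 per arm and 64 in total. Power at 32 per arm is 0.840.

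**Chance selections.** Expected false inclusions among 34 irrelevant candidates: 34 × 0.05 = 1.7, whether or not they are independent. Chance of at least one if independent: 1 − 0.95^34 = 0.825. Several items overlap (BMI and obesity; the side variables; linked dates; axillary surgery and nodes excised). With an assumed 20 to 25 effective candidates, the chance is 1 − 0.95^20 = 0.64 to 1 − 0.95^25 = 0.72.

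**Stage.** Suppose stage explains a share R² of outcome variance (an assumption; the protocol gives none). The noncentrality is 64·R²/(1 − R²): 3.37 for 5% and 7.11 for 10%. Stage would then reach p<0.05 in about 44% and 75% of trials.

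**Simulation.** 8,000 trials per scenario, 32 per arm, true difference 15 points, SD 20, a linear model with a single endpoint, and marginal screening of 34 covariates at p<0.05. The covariate structure is assumed: half continuous and half binary; either all noise or three prognostic (R² 0.30); mutual correlation 0 to 0.3. Unadjusted and fixed-list estimates were 14.9 to 15.1 throughout.

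| Covariates (correlation) | Screened on | Screened estimate | Power unadjusted | Power screened | Power fixed list |
|---|---|---|---|---|---|
| Noise (0) | outcome | 13.49 | 0.836 | 0.777 | 0.829 |
| Noise (0.2) | outcome | 13.71 | 0.838 | 0.782 | 0.831 |
| 3 prognostic (0) | outcome | 13.52 | 0.838 | 0.871 | 0.931 |
| 3 prognostic (0.1) | outcome | 13.62 | 0.842 | 0.875 | 0.930 |
| 3 prognostic (0.3) | outcome | 15.06 | 0.846 | 0.876 | 0.937 |
| Noise (0) | arm | 15.09 | 0.845 | 0.792 | 0.839 |
| 3 prognostic (0) | arm | 14.99 | 0.837 | 0.792 | 0.925 |

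Against the fixed list, outcome screening loses 4.9 to 6.1 points. A separate run with 35 candidates, two of them explaining 30% of variance, gave 89% against 93%, a loss of 4 points. Arm screening loses 4.7 points with noise and 13.3 with real predictors; the separate run gave 79% against 93%.

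Shrinkage in the first row is 1 − 13.49/14.94 = 9.7%. With no true effect, rejection rates of the screened models were 0.048 to 0.052 (outcome) and 0.042 to 0.053 (arm).

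Every scenario produced more than 2,300 different covariate sets in 8,000 trials. The most frequent set occurred in at most about 23% of them.

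**The case against.** The best defence is scope. The repeated measures comparison comes first and the regression is added to it, so nothing here touches the unadjusted comparison of volume over time. That stands. If normality fails, the only named substitute is Friedman's test, which compares time points rather than arms. The regression would then carry more weight, but the protocol does not say that it becomes the main analysis.

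Four stronger readings are tempting and are not supported.

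- *The rule biases the treatment effect toward zero.* The text does not say what the bivariate screen is run against. Shrinkage needs marginal screening on the outcome with weakly correlated covariates. It disappears with screening on arm imbalance and with prognostic covariates correlated at 0.3. It also disappears when treatment group is in the screening model: with 34 noise covariates (6,000 runs) the mean was 0.752 SD against 0.751 unadjusted, and power was 85% against 84%.
- *The rule costs power outright.* The loss is relative to a prespecified model. When outcome screening finds real predictors it beats no adjustment (0.871 against 0.838).
- *Type I error is inflated.* It reaches about 8% only if the best of the unadjusted and two screened models is reported, and the protocol plans no such choice.
- *Baseline significance tests are planned.* The text announces a comparability analysis and states no p values for it.

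Overlap also matters. With 20 to 25 effective candidates, shrinkage is about 6 to 8% and the power loss about 3 to 4 points. The simulation does not cover the Cox option.

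**Conclusion.** The concern holds for the additional adjusted regression. Its covariates would be picked by significance in the same 64 women from 34 partly overlapping candidates. About 1.7 false inclusions are expected if the candidates are irrelevant, with at least one in up to 83% of trials and in roughly 64 to 72% after a plausible allowance for overlap. Stage is not guaranteed a place, and baseline volume is not on the list.

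The cost against a prespecified model is about 4 to 6 power points if screening is on the outcome without regard to arm. It is about 13 to 14 points if screening is on arm imbalance and real predictors exist. Shrinkage of about 10% is conditional on outcome screening that ignores arm with weakly correlated covariates. These sizes rest on assumed covariate structures and a single-endpoint linear model. That the model depends on the sample does not rest on those sizes: it follows from the rule itself and appeared in every scenario tabulated.

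**What to change.** Replace the significance rule with one adjusted analysis of volume reduction whose covariates are fixed now: baseline volume and stage, kept whatever their p values. A few clinically chosen variables may be added if they are named in advance. The Background says "The most relevant risk factors are the number of lymph nodes excised in surgery, radiation therapy and obesity", but that concerns developing lymphedema, so the sentence alone does not establish them as predictors of volume response. State that the baseline comparability results will not be used to choose covariates, and label any other adjusted model exploratory.

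The cost is a change of wording; stage and volume are already collected. The downside is a few degrees of freedom. In the simulation, a fixed list of uninformative covariates lowered power from 0.836 to 0.829 at 32 per arm, and from 0.806 to 0.801 at 29 per arm.
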